#### Process evaluation

The process evaluation will consist of a validated satisfaction survey conducted with study participants at the 30-day follow up call. To further evaluate the trial, one on one telephone interviews will be conducted with trial participants, the SOLAR Team and members of the wider interdisciplinary team to ensure an in-depth evaluation of the process and impact of the trial within the ED and MAU and among study participants. A process evaluation protocol will be formulated to inform and underpin the methodology. Purposive convenience sampling will be utilised.

### Participant timeline {13}

The participant timeline is shown in Fig. 1

**Fig. 1 Fig1:**
[figure not shown]
Example template of recommended content for the schedule of enrolment, interventions, and assessments. Recommended content can be displayed using various schematic formats. See SPIRIT 2013 Explanation and Elaboration for examples from protocols. **List specific time points in this row. t1 Assessment. t2 Admission OR discharge. t3 30 day outcomes. t4 180 day outcomes

### Sample size {14}

We estimated the sample size based on the primary outcome (ED length of stay) using G*Power version 3.1. Using data from the Patient Experience Time (PET) database employed in the ED at UHL (unpublished data), the average ED length of stay for patients aged 75 and older for the 2019 yearly period was 18.63 h (standard deviation 19.91 h). Estimating a 50% decrease in ED length of stay in the intervention group (mean 9.31 h), and with a 20% attrition rate to follow-up, a sample size of 236 patients (118 in each group) will be required to achieve 90% power with two-tailed tests at an alpha level of 0.05.

### Recruitment {15}

Older adults (≥ 75 years) who screen positive for frailty with ISAR ≥ 2 will be asked if they would like to participate in the study by a dedicated research nurse during their ED or AMAU visit. They will be given an opportunity to read the information leaflet and ask questions before giving informed consent if agreeable. Participation is entirely voluntary.

## Assignment of interventions: allocation

### Sequence generation {16a}

Eligible participants will be block randomised in groups of 50 participants using a computer-generated 1:1 allocation through a Sealed Envelope website (www.sealedenvelope.com).

### Concealment mechanism {16b}

Allocation will be concealed from participants and researchers until both consent has been obtained and baseline evaluations has been performed. After allocation is revealed, the intervention will be organised by the team.

### Implementation {16c}

An independent website (sealedenvelope.com) will be used to generate the allocation sequence. The research nurse will enrol participants and assign participants to interventions once allocation has been revealed.

## Assignment of interventions: blinding

### Who will be blinded {17a}

The outcome assessor will be blinded to group allocation. Clinicians and patients will not be blinded to group allocation. The outcome assessor is not a member of the SOLAR clinical team.

### Procedure for unblinding if needed {17b}

There is no plan to unblind the outcome assessor.

## Data collection and management

### Plans for assessment and collection of outcomes {18a}

All participants will undergo a baseline assessment by the research nurse to include a global measure of function (Barthel Index) and quality of life (EuroQoL-5D [EQ-5D]).

Participants who are allocated to the SOLAR team CGA assessment and intervention will additionally be assessed by one or more members of the interdisciplinary SOLAR team who will complete a detailed clinical assessment including but not limited to managing medical issues and medication review, assessment of mobility and stairs, transfer, personal care, activities of daily living (ADLs), social supports, and cognition. Clinicians will be guided by their clinical expertise and codes of professional practice when completing the assessment.

Similarly, interventions prescribed by the SOLAR team will be based on subjective and objective assessment of patients and will include onward referral as appropriate. All assessments and interventions by the SOLAR team will be included in the medical chart, as is routine clinical practice to inform their medical care. Details of SOLAR assessment and intervention will be collected for the purposes of this study.

Data collection forms will be stored in a data repository and are provided as an appendix to this protocol. Hard copies of the consent form and completed questionnaires will be securely stored in a locked cabinet in a building requiring swipe card access.

### Plans to promote participant retention and complete follow-up {18b}

We will obtain multiple phone numbers for each participant to ensure complete follow-up. If participants are unable to answer, we will ring at a different time of the day and contact all available numbers. We will ask participants if they would like their next of kin to help with follow up phone calls and schedule phone interviews at their convenience. We will also reference hospital information systems during the interview so as to remind patients if they have had a hospital attendance. We will reschedule phone calls if the participant requests this.

### Data management {19}

#### Data entry

All relevant data entered by a research nurse will be stored on Excel and pseudo-anonymised. The key to this anonymisation will be kept by the Primary Investigator (PI). A quality check of 20% of data will be completed by an independent researcher. If there is more than 5% of errors identified across the data entry, all data will be independently checked by the second independent researcher.

#### Data storage

For the life of the study, the pseudo-anonymised data will be stored on an encrypted and password protected electronic data capture system (CASTOR). Each member of the research team designated the task of entering data will have their own unique login and password for this system. This data will be stored on an encrypted computer in a locked office in a building with restricted access.

Hard copies of the study materials will be stored in a locked cabinet in an office with restricted access for 7 years. Anonymised data will be made available on an open access platform (Open Science Framework) after study completion.

### Confidentiality {27}

The confidentiality of the data will be always ensured by the PI and all members of the research team. Identifiable data will not be disclosed to third parties, and no participant’s name will appear in any of the results, as indicated in the participant’s information leaflet. All researchers have completed Good Clinical Practice training.

Each participant in the study will be assigned a numerical code in order to link data collected at baseline to the data collected at follow-up at 30 days and 6 months. Aggregate data will be anonymised.

The research team will ensure anti-virus software is installed and up to date on all devices involved in data entry. All information trafficked from the clinical site to the research database will be pseudo-anonymised with unique study specific subject numbers. Access to the research database is managed by the principal investigator. No personal details or identifying data will be transferred from the hospital site to external sites, where the data will be analysed. Only coded/pseudonymised data will be transferred to external sites.

### Plans for collection, laboratory evaluation and storage of biological specimens for genetic or molecular analysis in this trial/future use {33}

There will be no biological specimens collected in this study.

## Statistical methods

### Statistical methods for primary and secondary outcomes {20a}

Appropriate descriptive statistics will be used to describe the baseline characteristics of study participants. These will include proportions, percentages, ranges, means and standard deviations and medians and interquartile ranges (where data are not normally distributed). We will analyse differences across the two groups for all continuous outcomes (ED length of stay, etc.) by using independent samples *t* tests with 95% confidence intervals. The non-parametric equivalent, the Mann-Whitney test, will be used for skewed data.

Incidence of ED return, unplanned hospital admission, nursing home admission and healthcare utilisation will be explored using crude and adjusted risk ratios with associated 95% confidence intervals using logistic regression. Unit costs will also be applied to resource use data. The total costs of health and social care input will be compared between groups with complete resource utilisation data, using non-parametric bootstrapping (it is anticipated that the data will be highly skewed in terms of distribution). A 5% level of statistical significance will be used throughout the analyses.

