**Methods:**

This will be a parallel 1:1 allocation randomised control trial. All patients who are ≥ 75 years will be screened for frailty using the Identification of Seniors At Risk (ISAR) tool. Those with a score of ≥ 2 on the ISAR will be randomised. The treatment arm will undergo geriatric medicine team-led CGA in the ED or Acute Medical Assessment Unit whereas the non-treatment arm will undergo usual patient care. A dedicated multidisciplinary team of a specialist geriatric medicine doctor, senior physiotherapist, specialist nurse, pharmacist, senior occupational therapist and senior medical social worker will carry out the assessment, as well as interventions that arise from that assessment. Primary outcomes will be the length of stay in the ED or Acute Medical Assessment Unit. Secondary outcomes will include ED re-attendance, re-hospitalisation, functional decline, quality of life and mortality at 30 days and 180 days. These will be determined by telephone consultation and electronic records by a research nurse blinded to group allocation.

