### Outcomes{12}

The primary outcome of the study is patient ED length of stay or Patient Experience Time (PET) time, which is recorded as time of arrival at the ED until discharge from ED to home or admission to a ward. For participants in the AMAU, this is defined as the time from arrival at the hospital to discharge from AMAU or admission to a medical ward.

Secondary outcomes include mortality, ED revisit, unplanned hospital visit(s) or nursing home admission within 30 days and 6 months of initial index visit. Healthcare utilisation will also be captured at 30 days (GP visit, Public Health Nurse visit, Allied Health Services) by telephone contact. Follow-up at 30 days and 6 months will be captured by telephone contact by a research nurse who is blinded to group allocation. Patient reported outcomes at 30 days include a global measure of function (Barthel Index) and quality of life survey (EuroQoL-5D EQ-5D) [13, 14]. In addition, patient satisfaction with their index visit will be explored using a patient satisfaction questionnaire. A detailed process evaluation will be completed using a mixed methods approach. The process evaluation will explore stakeholders’ experience of implementing the intervention as well as examining factors that enabled or hindered the delivery of same.

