### Methods in analysis to handle protocol non-adherence and any statistical methods to handle missing data {20c}

An intention to treat analysis using linear mixed models will be used to compare outcomes between the intervention and control arm and account for the correlation within-subject over time, while adjusting for differences in participant characteristics at baseline where appropriate. A sensitivity analysis, via multiple imputation, will be used to explore whether adherence to the intervention influences the effect of the intervention on the primary outcome.

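### The plan gives two unreconciled analyses for 30-day Barthel Index and EQ-5D, and neither guarantees adjustment for the baseline scores collected before allocation

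*Protocol article*

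**What the plan says.** All references are to the protocol article.

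- **Outcome named.** Abstract, Methods: "Secondary outcomes will include ED re-attendance, re-hospitalisation, functional decline, quality of life and mortality at 30 days and 180 days".
- **Instrument and time.** Outcomes {12}: "Patient reported outcomes at 30 days include a global measure of function (Barthel Index) and quality of life survey" (EQ-5D). No later time point is given for either instrument, and decline is not defined as a change or a threshold.
- **Baseline.** Section {18a}: "All participants will undergo a baseline assessment by the research nurse to include a global measure of function (Barthel Index) and quality of life" (EQ-5D). Under Concealment mechanism {16b}, allocation stays hidden until baseline evaluation is done, so both scores are proper pre-randomisation covariates.
- **First analysis rule.** Section {20a}: "We will analyse differences across the two groups for all continuous outcomes (ED length of stay, etc.) by using independent samples". The test meant is the t test, reported with a 95% interval. For data that are not normally distributed, the section adds: "The non-parametric equivalent, the Mann-Whitney test, will be used for skewed data". Adjustment is mentioned in this section only for the risk ratios.
- **Second analysis rule.** Section {20c}, on non-adherence and missing data: "An intention to treat analysis using linear mixed models will be used to compare outcomes between the intervention and control arm". The model is to allow for within-subject correlation over time, "while adjusting for differences in participant characteristics at baseline where appropriate". No outcome is named, and nothing says whether this replaces or supplements {20a}.

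**The concern.** Section {20a} is a positive rule covering every continuous outcome, not a detail held over for a later document. An analysis plan that follows it compares the 30-day Barthel and EQ-5D without the baseline scores. One that departs from it contradicts the published article. Section {20c} offers a different analysis of what must be largely the same outcomes, so the choice between an unadjusted test and a possibly adjusted model stays open until data are seen.

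The adjustment wording in {20c} is also loose. It refers to baseline differences and to appropriateness, which can be read as choosing covariates by the imbalance observed, and it does not name the baseline value of the outcome score. The Mann-Whitney fallback cannot take a covariate at all.

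At stake are the precision of the function and quality-of-life results, their exposure to chance imbalance at baseline, and clarity about which result answers functional decline. The primary outcome is not involved.

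**Working it through.** **1. The plan's own figure.** Sample size {14} gives a mean stay of 18.63 h, SD 19.91 h, intervention mean 9.31 h, 90% power, two-sided 5% and 20% attrition. The standardised effect is (18.63 − 9.31)/19.91 = 0.468. The exact t-test calculation needs 97 per group. Adding 20% gives 97 × 1.2 = 116.4, so 117 per group and 234 in total, within two patients of the stated 236. (Dividing by 0.8 instead gives 122 per group, 244 in total.) This figure rests on length of stay and does not change with anything below.

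**2. Patients with 30-day scores.** 118 × 0.8 = 94.4, so about 94 per arm, taking the plan's attrition figure as the loss at 30 days.

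**3. Standard errors.** In units of the outcome SD, the unadjusted standard error of the arm difference is √(2/94) = 0.146. Regression on the baseline score multiplies it by √(1 − r²), where r is the baseline to 30-day correlation. The article gives no r, so a range is shown. Power for an assumed true difference of 0.3 SD is Φ(0.3/SE − 1.96). The difference detectable with 80% power is (1.96 + 0.84) × SE.

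| r (assumed) | SE | SE reduction | Variance ratio 1/(1 − r²) | Power at 0.3 SD | Detectable at 80% power |
|---|---|---|---|---|---|
| unadjusted | 0.146 | – | – | 54% | 0.41 SD |
| 0.3 | 0.139 | 5% | 1.10 | 58% | 0.39 SD |
| 0.5 | 0.126 | 13% | 1.33 | 66% | 0.35 SD |
| 0.6 | 0.117 | 20% | 1.56 | 73% | 0.33 SD |
| 0.7 | 0.104 | 29% | 1.96 | 82% | 0.29 SD |
| 0.8 | 0.088 | 40% | 2.78 | 93% | 0.25 SD |

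The variance ratio is also the factor by which an unadjusted analysis would need more patients for equal precision.

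**4. Chance imbalance.** The baseline gap between arms has the same standard error, 0.146 SD. The probability of a gap above 0.2 SD in either direction is 2 × [1 − Φ(0.2/0.146)] = 0.17. With equal SDs, an unadjusted comparison carries r times the gap into the estimate: for a 0.2 SD gap, 0.06 SD at r = 0.3, 0.10 SD at r = 0.5 and 0.16 SD at r = 0.8.

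**5. Why the form of adjustment matters.** A change score has relative variance 2(1 − r): 1.40 at r = 0.3, 1.00 at 0.5 and 0.40 at 0.8. Regression on baseline gives 1 − r²: 0.91, 0.75 and 0.36. A change score is therefore less precise than the unadjusted test when r is below 0.5. With complete data at two time points and free arm means at baseline, the arm-by-time contrast of a mixed model equals the difference in mean change. So the mixed model in {20c}, left unspecified, does not secure the gain in the table even if it uses the baseline scores.

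**The case against.** The strongest reply is that {20c} already uses baseline. A model for within-subject correlation over time needs repeated measurements. Length of stay is recorded once, while Barthel and EQ-5D are taken at baseline and follow-up, so they are its natural targets. Confidentiality {27} also provides codes to link baseline with follow-up data. This stands to the extent that a reader who infers that the baseline scores go unused is claiming more than the article supports. It does not show that they will be used: the model names no outcome and no covariate, and has no stated rank against {20a}.

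Three other strong readings also fail.

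- *Decline is not measured.* A fall from 100 to 80 and a rise from 60 to 80 do give the same 30-day Barthel, but that concerns individuals. Change can be computed from the data collected. Under randomisation, the expected arm difference in mean 30-day score equals that in mean change. The Mann-Whitney test does not share this equivalence. Nor does {20a} name Barthel or EQ-5D, or say whether level or change is tested; they fall under it because it covers all continuous outcomes.
- *The t test is biased.* It is not. Its error rate and interval already allow for chance imbalance; the loss is efficiency.
- *The QALY result inherits the t test.* The Economic evaluation section describes incremental analysis and does not place QALYs under {20a}.

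It is also fair that these are secondary outcomes, that the gain depends on an assumed correlation and is small at 0.3, and that covariate lists are often left to an analysis plan. The last point does not cover two stated rules that differ.

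**Conclusion.** The point holds as one of reconciliation and precision on secondary outcomes, and it should be changed. Sections {20a} and {20c} prescribe different analyses for the 30-day Barthel and EQ-5D without ranking them, and neither guarantees adjustment for scores that every participant supplies before allocation. An unadjusted t test would be valid but would give up a standard-error reduction of about 5% at r = 0.3, 13% at r = 0.5 and 40% at r = 0.8. For a true difference of 0.3 SD, power would be 54% against 58%, 66% and 93%. These figures assume 94 per arm, a linear relation between baseline and 30-day score, and correlations and an effect size that the article does not give. The article supports no claim of bias, of unmeasured decline or of baseline data certain to be ignored.

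Two loose ends belong to the same point. Functional decline has no definition. The abstract's list reads as putting function and quality of life at 30 and 180 days, whereas Outcomes {12} gives Barthel and EQ-5D at 30 days only.

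**What to change.** 1. In {20a}, take the 30-day Barthel and EQ-5D out of the t test and Mann-Whitney rule. For each, name one primary analysis: linear regression (ANCOVA) of the 30-day score on arm and the same instrument's baseline score, with robust or bootstrap intervals to deal with skewness. The baseline score is always included.
2. In {20c}, say whether the mixed model is this analysis or a supportive one, and list the outcomes it covers. Drop any adjustment triggered by observed baseline differences.
3. State that the baseline-adjusted Barthel contrast answers the functional decline outcome.
4. Reconcile the 30- and 180-day time points in the abstract with Outcomes {12}.
5. As a secondary suggestion, adjust any QALY comparison for baseline EQ-5D utility.

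The cost is wording. No new data, visits or patients are needed, and the sample size stands. The one downside is that a missing baseline score needs a simple imputation, which should be rare because {18a} plans a baseline assessment for everyone.

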## Introduction

### Background and rationale {6a}

Ireland like many other countries has seen a steady increase in life expectancy and has an ageing population. By 2031, it is forecasted that there will be more than one million older adults in Ireland, representing an increase from 13% (2015) to 20% of our overall population [1]. According to the United Nations, the population over age 65 in Europe and North America is set to increase by 48% between 2019 and 2050 [2]. International evidence demonstrates that older adults account for up to 25% of all Emergency Department (ED) attendances and experience high rates of adverse outcomes following emergency care such as unscheduled ED return, unplanned hospital admission and functional decline [3, 4]. There is a paucity of research conducted to explore how comprehensive geriatric assessment (CGA) implemented in the ED may improve outcomes among those who present to the hospital for emergency care.

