### Trial design {8}

This study will be a parallel group randomised control trial with a 1:1 allocation ratio. In order to ensure standardised conduct and reporting, the Consolidated Standards of Reporting Trials (CONSORT) guidelines will be used [10].

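### The plan takes risk ratios for four secondary outcomes from logistic regression without naming how odds ratios become risk ratios

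*Protocol article*

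**What the plan says.** The Protocol article, section Statistical methods for primary and secondary outcomes {20a}, takes "Incidence of ED return, unplanned hospital admission, nursing home admission and healthcare utilisation" and says that these "will be explored using crude and adjusted risk ratios with associated 95% confidence intervals using logistic regression". The same section adds: "A 5% level of statistical significance will be used throughout the analyses".

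Section Outcomes {12} gives the time frame for the event outcomes: "Secondary outcomes include mortality, ED revisit, unplanned hospital visit(s) or nursing home admission within 30 days and 6 months of initial index visit". It places the telephone collection of healthcare utilisation at 30 days.

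The only other modelling statement is in the section on non-adherence and missing data {20c}: "An intention to treat analysis using linear mixed models will be used to compare outcomes between the intervention and control arm". Neither section names a log-link model or a standardisation step for the binary outcomes.

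On how common the events are, Background and rationale {6a} says only that older adults "experience high rates of adverse outcomes following emergency care such as unscheduled ED return, unplanned hospital admission and functional decline". It gives no figure.

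**The concern.** The sentence in {20a} fixes both an effect measure and a model, and the model does not give that measure directly. Logistic regression works on the log-odds, so its exponentiated treatment coefficient, and the interval around it, are on the odds ratio scale. An analyst who follows the sentence literally could fit the model, exponentiate the coefficient and put it in a column headed risk ratio.

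For a common outcome, that overstates benefit or harm. The population is selected for risk (age 75 or over, ISAR score of 2 or more), and the article itself expects ED return and unplanned admission to be frequent, so a visible gap is plausible. The odds ratio is also non-collapsible: crude and covariate-adjusted values differ even when randomisation has balanced the covariates. A crude and an adjusted estimate reported side by side under the wrong label could be misread as a sign of confounding. Finally, the article frames the existing evidence in risk ratios (readmissions RR 0.95, 95% CI 0.83 to 1.08), so a mislabelled odds ratio would be compared with it on a different scale.

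**Working it through.** The plan states no effect size or event rate for these outcomes, so there is no figure of its own to reproduce. The check sizes the gap between the two measures.

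**Inputs.** Measure and model: {20a}. Control risk p0: not given, so assumed from 5% to 50%. True risk ratio RR: illustrative values of 0.80 and 1.25.

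**Formula.** With p1 = RR × p0,

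OR = [p1 / (1 − p1)] / [p0 / (1 − p0)].

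**Worked example.** With p0 = 0.30 and RR = 0.80, p1 = 0.24. The odds are 0.24/0.76 = 0.316 and 0.30/0.70 = 0.429, so OR = 0.316/0.429 = 0.737.

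| Assumed control risk | OR when true RR = 0.80 | Apparent relative reduction (true 20%) | OR when true RR = 1.25 |
|---|---|---|---|
| 5% | 0.792 | 20.8% | 1.267 |
| 10% | 0.783 | 21.7% | 1.286 |
| 20% | 0.762 | 23.8% | 1.333 |
| 30% | 0.737 | 26.3% | 1.400 |
| 40% | 0.706 | 29.4% | 1.500 |
| 50% | 0.667 | 33.3% | 1.667 |

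The shift is away from 1 in both directions. At 5% to 10% control risk it is under 2 percentage points of relative reduction. At 20% it is about 4 points, and at 50% about 13.

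**Can a logistic model give the planned measure?** A simulated data set of 200,000 people had one prognostic covariate and a control risk of about 29%. Results:

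- Exponentiated logistic treatment coefficient, adjusted for the covariate: 0.61.
- Risk ratio from the same fitted model by marginal standardisation (mean predicted risk with everyone treated, divided by mean predicted risk with no one treated): 0.718.
- Crude risk ratio from the two observed proportions: 0.715.

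The standardised value agrees with the crude risk ratio; the raw coefficient does not.

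The same simulation shows non-collapsibility. The treated risk is 0.715 × 0.291 = 0.208, so the crude odds ratio is (0.208/0.792)/(0.291/0.709) = 0.64. The adjusted odds ratio is 0.61, although treatment was assigned at random.

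**The case against.** The strongest reply is that the sentence can be carried out correctly. The risk ratio is a sound target, and a logistic model reaches it through marginal standardisation, as the simulation shows. The crude risk ratio needs no model at all, because it is the ratio of two proportions. The text is a condensed article, its analysis plan is not shown, and the computing route is the kind of detail that such a plan supplies. This stands as a limit: the overstatement is conditional on raw coefficients being reported as risk ratios, and nothing in the article shows that this will happen. It does not remove the point, because the article is not silent. It names a measure and a model that do not match without a further step.

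The size also depends on unknown event rates. At 5% to 10% risk the gap is negligible, and nursing home admission may lie in that range.

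A reader might infer more than the article supports:

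- **That every binary secondary outcome is affected.** The sentence covers four outcomes. Mortality is a secondary outcome in {12} but is not in that sentence.
- **That the error carries into the economic evaluation.** That section uses costs, trial outcomes and EQ-5D-based QALYs in an incremental analysis, and {20a} bootstraps total costs. Neither feeds in a regression ratio.
- **That six-month service use is a common outcome at stake.** {12} collects healthcare utilisation at 30 days, and no frequency is given.
- **That the trial's main conclusion is at risk.** The primary outcome is length of stay and does not use this model.

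**Conclusion.** The mismatch is real and of moderate severity. The plan promises risk ratios from a model whose coefficients are odds ratios and names no conversion. If the coefficients are reported under the planned label, a true 20% relative reduction would read as about 21% to 22% at 5% to 10% control risk, 24% at 20% and 33% at 50%. The control risks are assumptions. The article's remark about high rates makes the upper part of the range plausible for ED return and unplanned admission but does not establish it.

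The consequence is confined to the size of the effect reported for the four named secondary outcomes. An odds ratio of 1 corresponds to a risk ratio of 1, and the two lie on the same side of 1, so the null hypothesis and the direction of effect are unchanged. The primary outcome and the sample size of 236 do not depend on this analysis.

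**What to change.** In {20a}, make the model match the measure. Any one of these will do:

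- Replace logistic regression with modified Poisson regression with robust standard errors, or with log-binomial regression.
- Keep logistic regression and state that risk ratios will be obtained from it by marginal standardisation, with bootstrap or delta-method confidence intervals.
- Keep logistic regression as it is and label the estimates as odds ratios.

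Either of the first two keeps the risk ratio that the plan already promises. The cost is one sentence and a different model call, or one extra post-estimation step, in the analysis code. No change to data collection or sample size is needed.
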